### **2.2 Secondary Objectives**

The secondary objectives of this study are to evaluate:

1. The effects of planning and SMS reminders on intentions, maintenance and recovery self-efficacy, action and coping planning and feedback of the intervention items.
2. The mediation effects of various constructs of the health action process approach (HAPA) Model (e.g. planning) on behaviour.

## **3. Study Design**

### **3.1. Design and Rationale**

This is a randomised, stratified between-groups study designed to assess the difference in saturated fat intake and coupon up-take between the three different experimental conditions; a) Planning and SMS reminders, b) Planning and c) Control Group. Subjects will be randomly allocated to one of these conditions and their responses will be measured by self-reported questionnaires.

Allocation to the subjects in the conditions will be stratified to balance by age group (30-45 years or 46-60 years), and gender. To help minimise any other imbalance effects obese (BMI $\geq$ 30) and non-obese participants (BMI $\geq$ 25), smokers and non-smokers will be also evenly allocated across the different cells.

## **4. Study Population**

### **4.1 Total Number and Nature of Subjects**

We will over-recruit at Time 1 to be able to take into account any drop-outs likely to occur over the study period. Seven hundred and fifty participants, who are motivated to make changes in their diet for a healthier cholesterol level will be recruited. Motivated subjects have been selected, since plans might sometimes fail to change behaviour if the individual does not hold sufficiently positive intentions to perform the planned behaviour (Prestwich et al, 2003; Sheeran et al, 2005).

Subjects will be recruited from both genders, be 30-60 years old with a BMI $\geq$ 25. Gender and age groups (30-45, 46-60 year olds) will be evenly distributed in the different cells. BMI will be split into two categories: a) overweight 25 $\leq$ BMI $\leq$ 29.9 and b) obese BMI $\geq$ 30.

Overweight and obese subjects have been selected, since they are expected to take into consideration their weight when making health-related judgements. They are more likely to consider themselves as being at higher risk than people of average weight (Renner et al, 2000) and therefore more likely to want to make dietary changes.

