##### **Exclusion Criteria:**

- BMI  $\leq$  24.9 (Body Mass Index)
- <30 years old
- >60 years old
- Pregnant women
- Diagnosed with cancer
- Diagnosed with an eating disorder
- Diagnosed with a heart-condition (heart-attack or angina)
- Any other chronic disease of the major organs (e.g. kidney failure)
- Not willing to sign online consent form
- Not literate in use of computer and the internet
- Not being able to print at home or at work
- Not having their own mobile phone
- Not capable of opening delivered SMS messages
- Not willing to receive SMS messages over the duration of the study

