### Conversion Chart

#### Length

1 inch = 2.5cm

1 foot = 30.48 cm

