#### Weight

1 ounce = 28.35 grams

1 pound = 453.6 grams

1 stone = 6.3503 kgs

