### Q6 BMI (HIDDEN QUESTION)

[Ordered/Single]

Answers

|       |    |      |
|-------|----|------|
| <25   | 1  | Excl |
| 25    | 2  |      |
| 26    | 3  |      |
| 27    | 4  |      |
| 28    | 5  |      |
| 29    | 6  |      |
| 30    | 7  |      |
| 31    | 8  |      |
| 32    | 9  |      |
| 33    | 10 |      |
| 34    | 11 |      |
| 35    | 12 |      |
| 36-40 | 13 |      |
| 40+   | 14 |      |

---

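### The screener's height chart gives an inch as 2.5 cm but a foot as 30.48 cm (2.54 cm per inch), so BMI can be overstated, usually slightly, for respondents who use the inch line

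*Protocol*

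**What the plan says.** Section 4.1 of the protocol sets the entry rule, "Subjects will be recruited from both genders, be 30-60 years old with a BMI $\geq$ 25", and the exclusion list in section 4.2 mirrors it with "BMI $\leq$ 24.9 (Body Mass Index". Section 4.1 also defines two BMI classes: "BMI will be split into two categories: a) overweight 25 $\leq$ BMI $\leq$ 29.9 and b) obese BMI $\geq$ 30". Section 3.1 wants these classes balanced across the conditions alongside smoking status ("smokers and non-smokers will be also evenly allocated across the different cells"), but words the pair as "obese (BMI $\geq$ 30) and non-obese participants (BMI $\geq$ 25".

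The rule is applied in the Appendix 5 screener. Q4 takes height as an open answer in metres, and Q5 takes weight as an open answer in kilograms. A hidden item, "Q6 BMI (HIDDEN QUESTION", turns these into a BMI code and excludes values below 25. A conversion chart stands directly after Q4 and Q5. Its length lines equate 1 inch to 2.5 cm and then state "1 foot = 30.48 cm". Its weight lines give an ounce as 28.35 g, a pound as 453.6 g, and "1 stone = 6.3503 kgs".

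**The concern.** The two length lines cannot both be right. The chart stands beside a question that accepts only metres, and some members of a UK panel will know their height in feet and inches. The resulting BMI is the only check on the BMI criterion that the protocol describes, and it also sets the overweight or obese class used for balancing.

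A short inch has an effect in one direction only: height comes out too low and BMI too high. It does not average out across respondents as ordinary rounding would. At stake are the stated population (some people just below 25 could be admitted) and the stated classes (some people just below 30 could be coded obese). Separately, the section 3.1 wording of the non-obese class has no upper limit. Read literally, every eligible participant meets it, including every obese one.

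**Working it through.** **Inputs.** From the Appendix 5 chart: inch 2.5 cm, foot 30.48 cm, ounce 28.35 g, pound 453.6 g, stone 6.3503 kg. From sections 4.1 and 4.2 and item Q6: BMI cuts at 25 and 30.

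**Is the chart consistent with itself?**
- Length: 30.48 / 12 = 2.54 cm per inch, against 2.5 stated. Conversely, 12 × 2.5 = 30.0 cm, against 30.48 stated. The inch figure is not reproduced.
- Weight: 16 × 28.35 = 453.6 g, and 6.3503 / 14 = 0.4536 kg per pound. These lines agree.

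**Effect on BMI.** BMI is weight divided by height squared, so the overstatement is (true height / charted height)² − 1. The true BMI that shows as a cut is the cut divided by (1 + overstatement). The result depends on how the respondent uses the chart.

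| Route | Charted height | BMI overstated by | True BMI shown as 25 | True BMI shown as 30 |
|---|---|---|---|---|
| Metres entered directly, or whole feet | exact | 0% | 25.00 | 30.00 |
| 5 ft 6 in, feet plus inches | 152.4 + 6 × 2.5 = 167.4 cm (true 167.64) | 0.29% | 24.93 | 29.91 |
| 5 ft 11 in, feet plus inches | 152.4 + 11 × 2.5 = 179.9 cm (true 180.34) | 0.49% | 24.88 | 29.85 |
| Any height, wholly in inches | inches × 2.5 | (2.54 / 2.5)² − 1 = 3.23% | 24.22 | 29.06 |

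Over 5 ft 0 in to 5 ft 11 in, the feet-plus-inches route averages 0.26%. Just outside that range, 4 ft 11 in gives 0.59%.

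**One person, two routes.** Take 5 ft 8 in and 73 kg. True height is 1.7272 m, so true BMI is 73 / 1.7272² = 24.47.
- Feet plus inches: 152.4 + 8 × 2.5 = 172.4 cm, and 73 / 1.724² = 24.56. Correctly excluded.
- Inches only: 68 × 2.5 = 170.0 cm, and 73 / 1.70² = 25.26. Wrongly admitted.

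**How many could be affected?** The protocol gives neither the panel's BMI distribution nor the use made of the chart. As an assumption, take panel BMI as normal with mean 26 to 28 and SD 4 to 6, and suppose that *every* respondent is affected to the same degree. With c the true BMI shown as 25, the share of those admitted whose true BMI is below 25 is P(c < BMI < 25) / P(BMI > c).
- Overstatement 0.25%: 0.5 to 1.0%.
- Overstatement 0.49%: 1.0 to 1.9%.
- Overstatement 3.2% (all inches): 6 to 11%.

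For example, with mean 27, SD 5 and c = 24.22, the share is (0.345 − 0.289) / (1 − 0.289), or 7.8% before rounding of the inputs. Any respondent who enters metres directly lowers these shares.

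**The case against.** The strongest reply is that the effect is trivial in practice. The chart prints a foot line, so the natural conversion is feet plus inches. On that route the largest height error is 11 × 0.04 = 0.44 cm, about 0.12 BMI units at 25. That is close to the 0.1-unit gap between the exclusion and inclusion wording, and similar to the effect of rounding metres to two decimals. Height and weight are self-reported in any case. Nothing obliges a respondent to use the chart, and the appendix is headed as a draft questionnaire. Section 11.1 names only age group and gender as stratification factors, and section 11.2 mentions modifiers without naming BMI. All of this stands and limits the weight of the point. It does not make the inch figure right, and unlike rounding the error has a fixed direction.

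A reader might infer that BMI is always overstated and that ineligible people make up as much as 6 to 11% of those admitted. The documents support neither reading. Direct metric entries and whole-foot heights carry no error. The higher share needs everyone to convert wholly in inches and rests on an assumed BMI distribution, so it is a hypothetical upper bound.

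On section 3.1, the reply is that the class is set against obese in the same phrase and section 4.1 gives its range, so the intent is clear. That is fair. Likewise, the apparent gap between 29.9 and 30 is one-decimal drafting, and Q6 codes whole units. Both are editorial.

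**Conclusion.** The point holds in limited form. The chart contradicts itself, and for respondents who use the inch line the error can only raise BMI. With feet plus inches it is 0 to 0.5% over the usual range of heights, moving the effective cuts to no lower than 24.88 and 29.85. It is 3.2%, with cuts of 24.22 and 29.06, only where the whole height is converted in inches. These figures follow from the chart alone. The number of people affected does not, because the protocol is silent on who uses the chart and how.

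Some people just below the entry criterion can therefore be admitted, and some just below 30 coded obese. A reader might go on to suspect a biased treatment effect. The documents do not support that: BMI is fixed at screening, before allocation, so the error favours no condition and balance on the coded class is unaffected. The consequence is a slightly looser population and class definition than the protocol states. It is worth correcting because the figure is plainly wrong, feeds the only BMI check described, and costs almost nothing to change.

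**What to change.** In the Appendix 5 conversion chart, give 1 inch as 2.54 cm. Alternatively, let Q4 accept feet and inches and have the script convert them, which removes the respondent's arithmetic altogether. Do this before screening opens: the screener keeps only the metric answer, so neither the original feet and inches nor the conversion route could be recovered afterwards.

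As a minor consistency edit, define non-obese in section 3.1 as 25 ≤ BMI < 30 and use the same cut in section 4.1.

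The cost is one figure in the script and one phrase in each of two sections, with no added subjects or analyses. The only downside is that slightly more panel members are screened out.

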#### **4.2 Subject Eligibility**

Subjects will be screened by use of an online questionnaire assessing weight/height, age, gender, pre-existing cardiovascular disease and cancer.

##### **Exclusion Criteria:**

- BMI  $\leq$  24.9 (Body Mass Index)
- <30 years old
- >60 years old
- Pregnant women
- Diagnosed with cancer
- Diagnosed with an eating disorder
- Diagnosed with a heart-condition (heart-attack or angina)
- Any other chronic disease of the major organs (e.g. kidney failure)
- Not willing to sign online consent form
- Not literate in use of computer and the internet
- Not being able to print at home or at work
- Not having their own mobile phone
- Not capable of opening delivered SMS messages
- Not willing to receive SMS messages over the duration of the study

##### **Inclusion Criteria**

- BMI  $\geq$ 25
- 30-60 years old
- Subjects of either sex can take part
- Not diagnosed with a heart-condition (heart-attack or angina)
- Not diagnosed with cancer
- Not diagnosed with an eating disorder
- Willing to sign the Informed Consent Form
- Computer and internet literate
- Being able to print at home or at work
- Having their own mobile phone
- Being capable of opening delivered SMS messages
- Be willing to receive SMS messages over the duration of the study

#### **4.3 Restrictions and Prohibitions**

There will be no restrictions or prohibitions placed once subjects have entered the main study-phase.

### **5. Study Treatments**

#### **5.1 Study Plan**

The flow of the different study phases is seen in Figure 1 below.

Figure 1 – Study Flow

[figure not shown]

## Phase 1

### a) Recruitment and Screening

Recruitment will be conducted by Virtual Surveys (<http://www.virtualsurveys.com/s>), an online recruitment agency, to cost effectively reach a specific target sample within the UK population. Virtual Surveys have their own online panel and a structured script will be used to screen individuals and exclude any people who do not meet the inclusion criteria (Appendix 5). Once subjects meet the inclusion criteria, they will be acquainted with the study procedures and asked to read an online informed consent form. They will be requested to click on a number of check boxes to make sure they have read and understood the information before they proceed to the online questionnaires. There will be two types of questionnaires at this phase: a) food frequency questionnaire and b) questionnaire focusing on social-cognitive determinants.

### b) Intervention

In the main study phase, subjects will be randomly allocated into one of three different conditions: a) Control Group, b) Planning and c) Planning and SMS Reminders. Subjects in the experimental conditions will be first provided with information on a healthy diet, the importance of good fats in a person's diet and the link between cholesterol, diet and overweight.

Subjects in the planning condition will then identify a list of situations where they would like to change their dietary intake. They will then be asked to match these situations with a list of behaviours. They would be requested to choose pairs of situations and behaviours that they want

to change rather than ones that they are already doing (Appendix 4). The list of behaviours is based on the process of change model of Prochaska (1979). It includes strategies such as counterconditioning, stimulus control and use of helping relationships. A number of more nutritionally based behaviours have also been created with the help of an expert nutritionist and information from accredited sources such as the Food Standard's Agency 'eat well, be well' site (<http://www.eatwell.gov.uk/>). Once, they have made their selections they will be given the option to go back to improve their plan or revise their situation-solutions.

Subjects in the SMS reminders and planning condition will also follow the same process to choose their situation-solution pairs and then be provided with SMS reminders of these pairs over the course of the 4 weeks. Two SMS reminders will be sent per week. Subjects will be able to choose the time of the day they would like to receive the SMS reminder. Subjects will be also informed that use of their mobile number for the SMS reminders will be made only during the duration of the study and they will not be contacted any further upon completion of the study.

All subjects will be invited to answer a number of questions on their perceptions of the information received, intentions to make lifestyle changes, feelings of self-efficacy. Subjects in the control group will be told that they will be put on a waiting list and will receive further information in four weeks time.

### **Phase 2 – Study End**

In the last phase, subjects will come back to the online study site to fill out a number of questionnaires. Subjects in the control group will at this stage be provided with the same educational information that the rest of the subjects received at Time1.

Upon completion of the study, all subjects will be thanked and debriefed (Appendix 7) and directed back to the Virtual Surveys site to receive payment (£15) for participation in the study.

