## 1.2 Rationale for Performing Study

The present study is an extension of a previous study conducted by Unilever Discover and approved by the Ethics Committee at the end of 2008. In this study we tested the effect of Heart-Age and the Planning tool on saturated fat intake. Heart-Age is a form of cardiovascular (CVD) risk communication. It is calculated as the age of a person with the same predicted risk but with all other risk factors levels in normal ranges. Heart-Age was found to be rather effective at helping people correctly perceive their CVD risk. Planning was more successful in changing behaviour e.g. lowering self-reported saturated fat intake. Effects were quite small in saturated fat changes and therefore it was necessary to start considering a) better measures of assessing behaviour changes and b) other ways of boosting the effects of implementation intentions on the outcome measures. This led to the present study, in which we combined planning with SMS reminders to test whether this could lead to stronger effects in behaviour than just planning on their own or nothing (Control Group).

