## 1.3 Brief Description of Intervention

To the best of our knowledge there are no studies that have tested online the combined effects of planning with SMS reminders in a more complex behaviour such as dietary changes. In the present study, the aim was to test for differences on the effects of three different conditions on saturated fat intake and the purchase of products that contribute to lowering or helping maintain a healthy diet.

At **Time 1**, subjects will be invited to participate in the study by an online recruitment agency, which will also carry out the screening process. Once, subjects have been accepted in the study they will be randomly allocated into one of three conditions. In the most advanced condition, subjects will be asked to form implementation intentions and be reminded of their plans by SMS reminders over the course of the two weeks. In the second condition, they will be asked to form plans on how to eat healthier over the course of two weeks. All conditions will be asked to fill out questionnaires on: a) a self-reported dietary intake questionnaire (Margetts et al, 1989) and b) a self-reported questionnaire on various social cognitive variables (e.g. intentions, self-efficacy). The Control Group (CG) will be only asked to fill out these questionnaires at this stage. All three groups will receive educational information on the importance of a healthy diet low in saturated fat and the association between high cholesterol and being overweight. A coupon of a cholesterol lowering product, with 50p off the face value, will be posted to all participants as a reward for successfully completing baseline assessments.

At **Time 2 (4 weeks later)**, subjects will be invited to fill out again the same dietary measures of food intake and an extension of the psychological determinants' questionnaire. Study subjects will be rewarded for their participation in the study (£15). This will be upon completion of study phase 2.

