### COPING PLANNING: Stage 1/2

|  |
|--|
|  |
|--|

| Have you thought about possible barriers that could interfere with eating a healthier diet? |            |             |             |              |
|---------------------------------------------------------------------------------------------|------------|-------------|-------------|--------------|
|                                                                                             | Not at all | Barely true | Mostly true | Exactly true |
| I have a detailed plan...                                                                   |            |             |             |              |
| How to avoid high-risk situations where the urge to eat unhealthy food is high              |            |             |             |              |
| How to arrange my daily routine to minimise the temptation to eat unhealthy food            |            |             |             |              |

## FEEDBACK QUESTIONS Stage 2

These two questions will be presented to subjects with the title 'Your Feedback'

| I found the information provided by the study so far: |                   |   |   |                |   |   |   |
|-------------------------------------------------------|-------------------|---|---|----------------|---|---|---|
|                                                       | Strongly Disagree |   |   | Strongly Agree |   |   |   |
|                                                       | 1                 | 2 | 3 | 4              | 5 | 6 | 7 |
| Trustworthy                                           |                   |   |   |                |   |   |   |
| Of personal relevance to me                           |                   |   |   |                |   |   |   |
| Enjoyable                                             |                   |   |   |                |   |   |   |
| Interesting                                           |                   |   |   |                |   |   |   |
| Contained a lot of new information                    |                   |   |   |                |   |   |   |
| Credible                                              |                   |   |   |                |   |   |   |
| Worrying                                              |                   |   |   |                |   |   |   |
| A wake up call                                        |                   |   |   |                |   |   |   |

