## **APPENDIX 8: EDUCATIONAL INFORMATION**

## WHAT'S THIS STUDY ABOUT?

By taking part in this study you will learn more about the importance of a healthier diet, good fats and maintaining a healthy cholesterol level.

You will follow each of the following steps:

**Step 1:** Find out more about a balanced diet

**Step 2:** The link between a balanced diet, fats and cholesterol

**Step 3:** Create a plan for a healthier diet and healthier cholesterol level

[figure not shown]

7%

next >>

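### The protocol contradicts itself on whether controls receive the education at Time 1; if they do not, neither contrast with control can be attributed to planning alone

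*Protocol*

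**What the plan says.** Two accounts of the control condition stand side by side.

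- **Section 1.3, Time 1 paragraph.** "All three groups will receive educational information on the importance of a healthy diet low in saturated fat". The same paragraph also says: "The Control Group (CG) will be only asked to fill out these questionnaires at this stage".
- **Section 5.1 b), Intervention.** "Subjects in the experimental conditions will be first provided with information on a healthy diet". Controls are told they will be "put on a waiting list and will receive further information in four weeks time". All subjects are nevertheless asked, in this phase, how they perceived the information they received.
- **Section 5.1, Phase 2.** The "control group will at this stage be provided with the same educational information that the rest of the subjects received at Time1".
- **Section 1.2.** The purpose is to see whether planning with SMS gives "stronger effects in behaviour than just planning on their own or nothing (Control Group").

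The aim in section 2.1 and the design factors in section 11.1 name Planning and SMS Reminders; education is not a factor. Section 11.3 bases the sample size on control versus planning. Section 7.1.2 lists reaction to the intervention as a secondary endpoint, and the Stage 2 feedback items in Appendix 3 begin "I found the information provided by the study so far".

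**The concern.** Whoever builds the web routing cannot tell from the protocol what a control subject should see at Time 1, and the answer determines what the trial estimates.

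If controls see the education, Planning v Control estimates the effect of adding planning. If they do not, it estimates the joint effect of education and planning against no information and a waiting-list message. There is no education-only arm, so no later analysis can separate the two parts. The education is also directed at the outcome: Appendix 8 advises cutting down on saturated fats, replacing butter and choosing low-fat dairy, which are the behaviours that the food frequency and portion-size questionnaires record. A positive result against control could then be reported as a planning effect when some or all of it came from the information pages.

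**Working it through.** **1. The passages set side by side.**

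| Place | Controls at Time 1 | Controls at Time 2 |
|---|---|---|
| 1.2 | described as nothing | not stated |
| 1.3, education sentence | education | not stated |
| 1.3, control sentence | questionnaires only | not stated |
| 5.1 b) | waiting-list message; education is assigned to the experimental arms | told to expect information in four weeks |
| 5.1 Phase 2 | none (the other subjects had it then) | education given |

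One sentence in 1.3 conflicts with the other four entries. It cannot easily be read as carrying no timing, because it sits inside the Time 1 paragraph.

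**2. What each contrast contains if 5.1 is followed.** Write E for education, P for planning, S for SMS.

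- Planning v Control: (E + P) − 0 = E + P
- Planning+SMS v Control: (E + P + S) − 0 = E + P + S
- Planning+SMS v Planning: (E + P + S) − (E + P) = S

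Here S means the addition of SMS to planning. Only the third contrast isolates a component, and it does so under either account, because both arms receive the education at Time 1.

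**3. The plan's own figures.** Section 6.2: 725 × (1 − 0.30) = 507.5, which agrees with roughly 500 at Time 2. Over three arms, 500/3 = 166.7, about 167 per arm. The figure of around 180 respondents in section 11.3 cannot be reproduced, since no effect size or SD is given. Solving d = (1.960 + 0.842) × √(2/n) backwards gives d = 0.295 SD if 180 is per arm, or 0.418 SD if it is the total (90 per arm).

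**4. How much education alone could produce.** The documents give no effect for the education, so a range is assumed, with P = 0.

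SE of a difference in SD units = √(2/166.7) = 0.1095. With λ = E/SE, the probability of a two-sided p < 0.05 is Φ(λ − 1.960) + Φ(−λ − 1.960).

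| Assumed E (SD) | λ | Probability that Planning v Control is significant |
|---|---|---|
| 0.10 | 0.91 | 0.150 |
| 0.15 | 1.37 | 0.278 |
| 0.20 | 1.83 | 0.447 |

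With 180 per arm the values are 0.158, 0.296 and 0.475.

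**5. What giving education to all arms could do to power.** Assume that the difference behind the 180 figure yields 80% power and that education supplied a share s of it. If controls also receive education, λ = 2.802 × (1 − s), whether 180 is per arm or in total. Power is then about 56%, 29% or 10% for s = 25%, 50% or 75%. The shares are assumptions, and the protocol does not describe the earlier study's control condition.

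**The case against.** The strongest reply is that the intention is clear enough. Section 1.2, the control sentence in 1.3 and both parts of 5.1 point to a control without information, and a waiting-list control is a recognised design. That stands: the comparator is not an error in itself. The defects are the conflicting sentence and the naming of the contrasts as if planning were the only difference.

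The reply also limits the scope. Planning+SMS v Planning is unaffected, and it addresses the new question in section 1.2 of whether reminders add to planning. This stands too, but the sample size in 11.3 rests on control versus planning, which is affected.

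Three stronger readings are tempting, and the documents do not support them:

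- *Controls are educated only after the final assessment, so the feedback endpoint cannot be compared with control.* Phase 2 mentions the education after the questionnaires but does not fix the order. The Appendix 3 feedback items are also Stage 2, so controls might or might not have seen the information when they rate it. The order needs stating. It cannot be assumed.
- *Controls would be prompted to plan by the Appendix 8 opening screen*, whose third step is "Create a plan for a healthier diet and healthier cholesterol level". Nothing says controls would see that screen unchanged. It matches the Step 3 heading in Appendix 4 and fits pages built for the planning arms. It matters only if the same pages are reused for controls.
- *The test has a false-positive rate of 15% to 45%.* If education shifts the outcome and only one arm receives it, the arms truly differ. The percentages are power to detect that difference. The fault lies in the attribution.

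**Conclusion.** The contradiction is real and should be resolved before launch, because it cannot be repaired once data are collected. Under the account that most of the text supports, a difference from control cannot be attributed to planning alone; the contrast between the two active arms remains clean.

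The size of the problem depends on the unknown effect of the education. The figures of 15%, 28% and 45% assume shifts of 0.10, 0.15 and 0.20 SD, 167 per arm and no planning effect. That last assumption is an extreme case, since section 1.2 reports that planning lowered self-reported saturated fat intake in a previous study. The figures show that modest education effects could produce a significant result on their own; they do not predict that this will happen.

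**What to change.** Reconcile section 1.3 with section 5.1 b) and Phase 2, define the control condition once, and refer to that definition elsewhere. Then follow one of two routes.

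**If controls get no education at Time 1:**
- Word the objectives and conclusions for both control contrasts as *education plus planning (with or without SMS) versus no information*.
- Name Planning+SMS v Planning as the contrast that isolates SMS.
- State that controls receive the education after all Time 2 questionnaires, and leave them out of the comparison of feedback on the information.

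This costs wording and page order only.

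**If all arms get the education at Time 1:**
- Remove the waiting-list message, and remove the plan step from the control version of the screens.
- Recheck the 180-respondent figure, because the contrast with control may be smaller than the one it was based on.

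This costs wording, routing of existing pages and possibly a larger sample. In return, Planning v Control becomes a test of planning. It changes the comparator that most of the protocol describes, so it is a design choice for the sponsor and not a mere correction.
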